#### Process evaluation

Technical feasibility and acceptance of the TeleKasper app within the network will be thoroughly evaluated. Parameters of the TeleKasper app usage will include the number of times the app is used by users, frequency of clicks indicating the use of specific app components or sections, frequency of query generation, time taken to answer different types of queries, and rate of reads of specific articles in educational offers. We will also assess the average number of clicks per user. Users will be categorized according to the frequency of use and underlying factors of use will be evaluated. Feedback questions will be asked upon successful completion of Tele-Konsil and Tele-Info to assess query complexity and satisfaction with recommendations related to infectious disease care. The analysis will be performed for the entire network. Subgroup analysis will be performed to evaluate differences between hubs, hospitals, and months during the intervention phase, when appropriate. Users will also be provided a LimeSurvey questionnaire to evaluate the reasons of use and/or no-use of the TeleKasper app.

As part of the process evaluation, an economic evaluation will also be performed comparing cost and cost savings at the hospital level with the costs for providing the novel telemedical ID consult service.

### Sample size and power calculation

For the sample size calculation, we assumed a lead-in phase of 2 months, a stepped wedge phase of 24 months, and a follow-up phase of 3 months. If 35 hospitals are included, assuming an intervention effect of a 20% reduction in antibiotic consumption, and assuming that 60% of the variance in the hospitals’ monthly consumption data is explained by hospital effects, this would result in a power of 83%. Due to a lack of information, possible effects of seasonality are not considered in the power calculation. However, the stepped wedge design allows this to be taken into account in the statistical analysis. With an effect of 20%, a study with 36 hospitals has a power of 84%, and with 32 hospitals 78%. With the 33 participating hospitals the power would be almost 80%.

### Statistical analysis

#### Primary outcome analyses

The primary outcome DDDs per 100 patient days will be measured monthly and analyzed using a Poisson mixed-effects model with an intention-to-treat analysis. The intervention, seasonal effects, and calendar time will be included as fixed effects, and the hospitals will be included as a random effect. Data from the transition phase will be excluded from the analysis. Results will be reported as rates per 100 patient days with 95% confidence intervals.

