### Outcome measures and their assessment

#### Primary outcome

The primary outcome of the study is the antibiotic consumption. This will be measured using defined daily dose (DDD) per 100 patient days. The data will be provided by the hospital pharmacy using anonymized routine electronic health records. In addition, an analysis is also possible for individual departments of the pediatric hospital. All systemic antibiotics will be included according to the second level of the WHO Anatomical Therapeutic Chemical (ATC) classification system for antimicrobials (J01) [17], as well as the substances rifampicin (J04AB02), oral vancomycin (A07AA09), fidaxomicin (A07AA12), and metronidazole (P01AB01). As part of the data management process, an attempt will be made to identify extreme values and, if necessary, corrections will be made in consultation with the corresponding hospital. As the data are part of routine health data, information should not be missing. Nonetheless, missing data will not be imputed or replaced.

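### The primary Poisson model sets the within-hospital variance of monthly DDDs equal to their mean, so the 95% CI for the intervention effect is not calibrated to the data

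*Protocol article*

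**What the plan says.** The section on the primary outcome defines antibiotic consumption from pharmacy data: "This will be measured using defined daily dose (DDD) per 100 patient days". The section on primary outcome analyses adds that "The primary outcome DDDs per 100 patient days will be measured monthly" and that the data will be "analyzed using a Poisson mixed-effects model with an intention-to-treat analysis". On the terms of the model it says "The intervention, seasonal effects, and calendar time will be included as fixed effects", and "the hospitals will be included as a random effect". It names no other random term, no dispersion parameter and no robust variance. On reporting it says "Results will be reported as rates per 100 patient days with 95% confidence intervals". The DDD-based secondary outcomes are to be analysed in the same way.

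The sample size section plans for a 20% reduction and takes 60% of the variance in hospitals' "monthly consumption data is explained by hospital effects". That leaves 40% as variation within hospitals. It gives no SD or CV, and it says that seasonality was left out of the calculation.

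**The concern.** A DDD is an amount of drug divided by a reference dose. One course of treatment can contribute several DDDs or a fraction of one, and courses cluster in outbreaks, so the Poisson relation of variance to mean has no basis here. The hospital intercept absorbs differences between hospitals. The fixed effects absorb season and trend that hospitals share. All other month-to-month variation within a hospital is assumed to have Poisson size, whatever the data show. The article's discussion describes a post-lockdown rebound, a record RSV season and antibiotic shortages. Where these hit hospitals differently, shared time terms cannot absorb them.

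The trial aims to show superiority, and the interval for the intervention effect carries that claim. If its width is wrong, so is its coverage.

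**Working it through.** **1. What the stated power implies.** Inputs from the sample size section: 35 hospitals, 2 + 24 + 3 = 29 months, 20% reduction, between-hospital share 0.6, power 83%. Assumed: two-sided 5% (from the 95% CI), fixed month effects, transition month dropped as the analysis section says.

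- Implied SE = effect / (1.960 + 0.954). On the log scale: 0.2231 / 2.914 = 0.0766. On the relative linear scale: 0.20 / 2.914 = 0.0686.
- The generalised least squares variance of the effect comes from a within-hospital covariance of total variance × (0.4 I + 0.6 J), where I is the identity matrix and J the matrix of ones. I solved for the total CV that gives this SE; residual CV = total CV × √0.4.
- Starts spread over 22-24 months: residual CV 0.58-0.66. Four hospitals per month (one per hub): 0.40-0.45. Keeping the transition month, or leaving out time effects, gives higher values.

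The 83% itself cannot be reproduced without an SD. With the CV fixed to give it, the 24-month spread yields about 80%, 81% and 84% at 32, 33 and 36 hospitals, against the stated 78%, almost 80% and 84%. Four per month yields 75%, 78% and 85%. The first set is the closer match, but neither roll-out is excluded.

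**2. What a Poisson model can reproduce.** Its residual CV is 1/√mean. A CV of 0.40 needs a mean of 1/0.40² = 6.3; a CV of 0.66 needs 1/0.66² = 2.3. So the variability behind the power statement fits the analysis model only at about 2-6 units per hospital-month.

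**3. Size of the error.** Let CV be the total residual CV and m the mean of whatever is modelled. Then true SE / model SE = f = CV × √m, and type I error = 2 × (1 − Φ(1.96 / f)), taking months as independent. The article gives neither quantity, so all values are assumptions.

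*Monthly totals with a patient-day offset:*

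| Mean | CV 0.10 | CV 0.15 | CV 0.25 |
|---|---|---|---|
| 200 | f 1.41, 17% | f 2.12, 36% | f 3.54, 58% |
| 400 | f 2.00, 33% | f 3.00, 51% | f 5.00, 70% |

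*Rate per 100 patient days as the response:*

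| Rate | CV 0.10 | CV 0.15 | CV 0.25 | CV 0.40 |
|---|---|---|---|---|
| 20 | f 0.45, <0.1% | f 0.67, 0.3% | f 1.12, 8% | f 1.79, 27% |
| 60 | f 0.77, 1% | f 1.16, 9% | f 1.94, 31% | f 3.10, 53% |

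In the second reading the interval also depends on the reporting unit. The same data per 1000 patient days would give an interval 1/√10 = 0.32 times as wide. With totals and an offset, the reporting unit has no effect on the width.

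**4. Simulation check.** 33 hospitals, no true effect, hospital, month-of-year and linear time effects, 400 runs per cell. Here the CV is the variation added on top of Poisson, so f = √(1 + CV² × m). At mean 200 and CV 0.2 the formula gives f = 3.0 and 51%; the simulated Poisson type I error was 56-57%. At mean 30 and CV 0.2 the formula gives 19%; the simulation gave 18-19%. With an estimated dispersion factor the error was about 5-8% in nearly all cells; one cell gave 11.5%.

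**The case against.** A reader might infer that the interval is bound to be far too narrow and that a trial without effect would often be declared positive. The article does not support that as a general statement. It does not say whether totals with an offset or rates are the Poisson response, and its wording fits either. With the rate as response and a residual CV of 10-15%, the interval can be too wide. The unit dependence belongs to the rate reading only, and the highest error rates at CVs of 10-25% belong to the totals reading only; the two cannot be added together.

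A reader might also infer that the model has no term for the 40% of variance within hospitals. That goes too far. Since the power calculation ignored seasonality, part of the 40% may be seasonal or secular variation that the planned fixed effects remove, and the Poisson model has a residual variance of its own. For the same reason the back-solved CV may overstate what remains after adjustment.

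Finally, this is a condensed article, and the SAP, which is not at hand, may already contain a dispersion term or robust standard errors. That is possible. But the article does more than stay silent on a detail: it names the distribution and the random effect, and followed as written they give an interval that does not respond to the observed scatter. That part of the concern stands.

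**Conclusion.** The defect is in the stated method: the within-hospital variance is fixed by the mean, so the 95% CI for the intervention effect is not calibrated to the data. Direction and size depend on quantities that the article does not give.

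- Totals with an offset, assumed mean 200-400, residual CV 10-25%: interval too narrow, type I error about 17-70%.
- Rate as response, assumed 20-60: too wide at a CV of 10%; too wide to mildly too narrow at 15% (0.3-9%); too narrow from about 25% (8-31%).
- At the residual CV of about 0.4-0.66 implied by the stated 83% power: too narrow for any mean above about 6, under either roll-out.

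The last result uses the plan's own figures, with the caveat that some of that CV may be seasonality. The analysis section mentions confidence intervals and no p-value; type I error here means that the 95% CI excludes a rate ratio of 1. The point should be settled before the primary analysis.

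**What to change.** Keep the log-linear mean model. State that the response is monthly DDDs with log(patient-days) as offset, which removes the dependence on the reporting unit. Estimate the dispersion by quasi-Poisson, negative binomial or a hospital-by-month random effect. Take the primary 95% CI from hospital-clustered standard errors with a small-sample correction for 33 clusters. Do the same for the secondary DDD outcomes.

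The clustered standard errors also protect against correlation between months. In a simulation with 33 hospitals, 29 months, 100-700 DDD per hospital-month and an assumed monthly autocorrelation of 0.4, quasi-Poisson alone still gave a type I error of 15-20%, and clustered standard errors gave 3-5%. The autocorrelation is an assumption; with independent months an estimated dispersion removes most of the problem by itself.

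The cost is a sentence or two in the analysis plan and standard R code, with no new data. The downside is that the interval will usually be wider. If the SAP already contains these elements, it is enough to make the description of the primary analysis agree with it.

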#### Secondary outcomes analyses

The secondary outcome using DDD per 100 patient days will be analyzed with an analogous approach as the primary outcome. Full information on subgroup analyses of the antibiotic consumption data is provided in the Additional file 2. The other secondary outcomes, including process evaluation parameters, will be analyzed using descriptive statistics. If applicable, the primary method for binary outcomes will be logistic regression and for continuous outcomes linear regression. Data will be analyzed using R software, version 4.2 or higher [19].

### Ethical approval

This study is approved by the ethical committee of the Ludwig Maximilians University under project number 21–0500. The study is registered at the German Clinical Trials Register (DRKS) portal under trial number DRKS00028534.

### Protocol modifications

Any modifications to the protocol will require a formal amendment to the protocol. All protocol modifications will be reported to the sponsor. Such an amendment must be approved by the relevant ethics committee prior to implementation and will then be communicated to the participating non-university hospitals.

## Discussion

Antibiotic consumption in pediatric hospitals is high. ASPs have been shown to reduce antibiotic consumption. This study is a novel approach to implementing an ASP in non-university children’s hospitals by using telemedical means and an innovative app. It is the first nationwide study including 33 non-university hospitals in four different demographic regions in Germany.

This study faced substantial unpredictable challenges and respective evaluation will have to try to account for the effects due to these influencing factors. The COVID-19 pandemic and the associated non-pharmaceutical measures, i.e., lockdown periods, had a notable impact on the incidence of infections, particularly respiratory infections. Once lockdowns had been lifted, both adult and pediatric populations experienced a massive rebound in infections, as described in several publications, including in those from our group [20, 21]. The year 2022 witnessed the most severe RSV season ever to be recorded in Germany as well as in other countries. The severity of the disease led to a substantial increase in antibiotic prescriptions, particularly in very young children [20, 21]. This situation was aggravated by substantial shortages in key antimicrobials both in 2022 and 2023. Subsequently, these shortages affected many first-line antibiotics, such as oral formulation of amoxicillin, jeopardizing any efforts to follow the project’s proposed first-line treatment regimens for a number of pediatric infectious diseases such as otitis media, community-acquired pneumonia or streptococcal pharyngitis.

## Trial status

The randomization of sites was performed in February 2022. The study is currently ongoing, the intervention phase is set to end in March 2024. The last patient for telemedical consultation (Tele-Konsil) will be recruited by June 30th, 2024 (“last patient in”). The team responsible for the study consists of physicians who work as infectious disease experts and were deeply involved in addressing patients’ health needs during the COVID-19 pandemic. Although the plan was to submit the protocol manuscript earlier, competing priorities led to inevitable delays in submission. Protocol Version: 2.0

## Data Availability

The consortium will have access to the final data. Results and findings of the study will be released through publications in the scientific literature and conference presentations.

## Abbreviations

AMR: Antimicrobial resistance
ASP: Antibiotic stewardship program
ATC: Anatomical Therapeutic Chemical
DDD: Defined daily doses
IDSA: Infectious Disease Society of America
PPS: Point prevalence studies
TDM: Therapeutic drug monitoring
WHO: World Health Organization
